### Intervention

In this study, the interventions will consist of two mutually exclusive conditions for the teachers or parents: a) ICC-T – the intervention for teachers which will consists of a five-day-training (8 h per day) or b) ICC-P – the intervention for parents which will consist of a three-weekend-day consecutive training session (8 h per day) and a fourth day as a refresher day six weeks later. The ICC-T and ICC-P training concepts are based on the childcare guidelines of the American Academy of Pediatrics [58] and Dreikurs et al. [59]. The ICC program offers participants (parents & teachers) a basic training in essential interaction competencies with children. The intervention focuses on non-violent interaction strategies and on encouraging warm, sensitive, and reliable adult–child relationships [41]. ICC-P is an adapted version of ICC-T, shifting from school to family context [53] with the aim to achieve the greatest possible agreement in content between ICC-T and ICC-P. It has been successfully field-tested [53].

ICC-T [3, 38, 39, 42] and ICC-P [53] aim to prevent harsh and violent discipline in school and home settings respectively by improving the relationship between children and teachers as well as children and parents, by confronting and altering the teachers’ and parents’ favorable attitudes towards violence and enabling them to use non-violent discipline strategies. ICC-T and ICC-P follow four key principles which guide the implementation: 1. Participative approach: teachers and parents are encouraged to contribute actively in the training; 2. Confidential workshop atmosphere: participants can freely reflect and share their daily challenges, needs, and personal experiences in dealing with children’s behavior; 3. Intensive practice combined with theoretical inputs: parents and teachers practice to integrate the learned skills into their daily interactions; 4. Training sustainability with various activities including repetition of the content, self-reflection of personal experience, team support and peer support groups, networking and ongoing supervision. These key principles guide the ICC-T and ICC-P training workshops that focus on five core components (c.f., Table 2).

**Table 2 Tab2:** Descriptions on intervention modules

Brief name	1. Interaction Competencies with Children – for Teachers (ICC-T) 2. Interaction Competencies with Children – for Parents (ICC-P)
Rationale, theory, & goals	Maltreatment prevention and improvement of adult–child relationship; based on attachment, behavioral, and social learning theories and the guidelines set forth by the American Academy of Pediatrics [58]; violence prevention components were grounded in the work of Dreikurs et al. [59]
Materials	The ICC-T manual^a^ with the respective materials (including facilitator instructions, handouts, theoretical inputs, instructions for discussions, & role-plays) is freely available. The ICC-P manual is currently under development and can be requested by the authors
Procedure	1. ICC-T begins with a welcome session in which the expectations, wishes, and concerns of the trainees are explored. Five core components form the content of ICC-T: teacher-student interaction (3 sessions at 90 min), maltreatment prevention (5 sessions at 90 min), effective discipline strategies (8 sessions at 90 min), supporting burdened students (2 sessions at 90 min), and implementation (2 sessions at 90 min). Participants form peer support groups and are invited to seek advice from trainers virtually if needed. At the beginning and the end of the training, teachers are asked to evaluate the feasibility of the intervention. A participation of four entire days leads to certification of attendance 2. ICC-P begins with a welcome session in which the expectations, wishes, and concerns of the trainees are explored. Four core components form the content of ICC-P: adult–child interaction (3 sessions at 60–90 min), maltreatment prevention (4 sessions at 60–90 min), effective discipline strategies (7 sessions at 60–90 min), and implementation (1 sessions at 90 min). A refresher day after 6 weeks enables practice, repetition, and exchange with peers and trainers. The participants form peer support groups and are invited to seek advice from trainers virtually if needed. The first two days are conducted in same gender groups, the third day and the refresher days in mixed gender groups. At the beginning and the end of the training, parents are asked to evaluate the feasibility of the intervention. A participation of 3 out of 4 days (including the refresher day) leads to certification of attendance
Provider	Two trainers with background in psychology and/or teaching per school
Location	At the premises of the selected schools
Duration	1. ICC-T: 5 days (8.5 h per day) 2. ICC-P 3 days + 1 refresher day (8 h per day)
Tailoring	Tailoring is one of the key principles of ICC intervention modules: Trainees are invited to actively participate, tailor the program, and develop their own strategies for implementing the training content in their daily work with flexibility and fidelity
Modifications	There are no modifications of the intervention
Fidelity	To increase fidelity comprehensive materials are provided. Trainers apply all the required materials

*Note.* The described intervention modules have been adapted from the Template for Intervention Description and Replication (TIDieR) checklist [60]. For detailed intervention descriptions: c.f., Kirika & [name] [41]; Kabelege et al. [53]

^a^The *ICC-T* training manual is available at [61]

#### Intervention procedures

Trained facilitators with well-defined background in psychology and adult-teaching will implement the ICC-T and ICC-P interventions within the premises of the selected schools. Eligible research assistants will work closely with trainers throughout the intervention. Participation in ICC-T and ICC-P respectively will be free of charge for all participants. Participants will be provided with food (breakfast & lunch) and beverages during training. Information explaining in detail the training procedure and topics will be given to each participant.

The training of parents will take place over three consecutive Saturdays and one refresher day delivered after six weeks. ICC-P will be implemented for both female and male parents in groups of 20 to 25 participants. The parents will be individually invited for training and will have gender-separate workshops on the first two workshop days with the intention to maximize participation of female and male parents [62] and to encourage parents to freely express their beliefs about discipline measures used with their children. On the third and fourth day, female and male parents will participate jointly in one training group as they will be trained on alternative discipline and good parenting skills. Teachers from the selected schools will be trained in ICC-T in groups of approximately 25 participants on five consecutive days in a week during school holidays in 2024. All trainings will take place within school premises.

To monitor the fidelity, acceptability, and feasibility of the training, a process evaluation will be conducted during the training sessions of ICC-T and ICC-P. The process evaluation will utilize standardized evaluation forms completed by trained research manager observing the program sessions (rating participants’ engagement & facilitators’ performance) and standardized reflection forms completed by facilitators after each session (rating their satisfaction with the session and specific activities covered). Furthermore, for each training day, five randomly selected participants will be asked to fill out a purpose-built questionnaire on their perceived comprehension of that day’s training content and the method used by the facilitator for delivering the content during that day. At the end of the workshop, all participants will evaluate the session content, the methods used, and the performance of trainers using a standardized questionnaire.

The participants’ experiences with and thoughts on the intervention will be assessed in one focus group discussion (FGD) with 10 parents after the refresher day and one FDG with 10 teachers two weeks after the implementation and one FGD with all facilitators after the completion of all intervention workshops. Ten in-depth interviews with five teachers or parents who have reported decreases in violence perpetration post-intervention and five teachers or parents who have reported no changes (or even increases) in violence perpetration. The FDGs and in-depth interviews will be audio recorded.

#### Control

There will be no training delivered to participants from control schools. Data will be assessed at baseline and follow-up with the same procedure in control and intervention schools. During the present study, the control schools will not be part of any other, similar interventions.

### Outcomes

Quantitative data will be collected to investigate the effects of ICC-T and ICC-P on the teachers’ and parents’ use of violence against children in home and school. As primary quantitative outcome, violence by teachers in school and by parents at home will be assessed. The secondary quantitative outcome measures include parents’ and teachers’ favorable attitudes towards violence, children’s mental health problems, children’s quality of life, peer violence experienced by children, parent–child relationship and teacher–child relationship, perceived stress of all participants, school climate experienced by teachers, teachers’ self-efficacy, teachers’ decision making, teachers’ and parents’ normative beliefs about violence, and intimate partner violence experienced by female parents. All primary and secondary quantitative outcomes will be collected at baseline and follow-up data assessment. In addition, socio-demographic data on participants’ age, gender, and living situation will be assessed. Apart from this, children will be asked to identify the two most caring persons for them personally and parents and teachers will be asked on their household earnings.

Qualitative information will be collected to complement the quantitative data with FGDs and in-depth interviews for process evaluation and qualitative end-line evaluation. A process evaluation will be conducted to assess the quality and fidelity of the implementation of the intervention, participants’ engagement with the intervention, and whether the intervention achieved its goals in terms of its primary and secondary quantitative outcomes. The FDGs will assess the parents’ and teachers’ experiences with and thoughts on the intervention. The in-depth interview will assess parents’ and teachers’ perceived improvement of violence reduction. For qualitative information on process evaluation, standardized evaluation as well as reflection forms will assess the staff members’ experiences with conducting the intervention.

#### Primary quantitative outcomes

##### Parental violence

The use of emotional and physical violence by parents against children at home will be measured with adapted versions of the Conflict Tactics Scale (CTS) [3, 63, 64], on the one hand by children’s self-reported violence experiences and on the other hand by parents’ self-report on the use of violence. For the present study, the CTS will include 9 items on experienced physical violence, 7 items on experienced emotional violence, and 5 items on emotional maltreatment. The items will be answered on a 7-point Likert scale ranging from 0 (this has never happened in the past week) to 6 (not past week, but before). CTS-scores on emotional and physical violence will be derived by summing up the respective item scores, whereby higher scores indicate higher levels of parental violence. A previous study in Tanzania assessed parental violence with the adapted CTS versions and revealed good psychometric properties [53].

In addition, during the quantitative interview 4 CTS-items will be body mapped by asking the children where on their body they experienced the emotional (shout & call dumps) and physical (hit & slap) violent act by parents. The affected body parts will be documented on a sheet of paper with a body-icon. Promising results for body mapping have been shown for trauma research in the context of refugees [65].

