##### Teachers’ violence

An adapted version of the CTS [3, 63, 64] will be used to assess the emotional and physical violence by teachers at school, captured through both children’s and teachers’ self-reports. The CTS will include 9 items on physical violence, 7 items on emotional violence. For children’s report, 2 additional purpose-built items on witnessed violence by teachers will be assessed. The teacher version uses the same answer scale and scoring as the CTS versions for parental violence (c.f., for more details outcome description about parental violence). Previous studies in East Africa assessing teachers’ violence revealed acceptable psychometric properties [14, 66, 67].

In addition, during the quantitative interview 4 CTS-items will be body mapped by asking the children where on their body they experienced the emotional (shout & threaten) and physical (hit & pinch) violent act by teachers. The affected body parts will be documented on a sheet of paper with a body-icon. Promising results for body mapping have been shown for trauma research in the context of refugees [65].

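### The primary violence score gives its top code, 6, to acts absent from the past week, so the score can rise when violence stops

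*Protocol article*

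**What the plan says.** In the protocol article, under Primary quantitative outcomes, Parental violence, items are "answered on a 7-point Likert scale ranging from 0 (this has never happened in the past week) to 6 (not past week, but before". The scale has "9 items on experienced physical violence, 7 items on experienced emotional violence, and 5 items on emotional maltreatment". Two reporters are used: "on the one hand by children’s self-reported violence experiences and on the other hand by parents’ self-report on the use of violence". The scoring rule is "CTS-scores on emotional and physical violence will be derived by summing up the respective item scores, whereby higher scores indicate higher levels of parental violence".

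Under Teachers' violence the link is explicit: "The teacher version uses the same answer scale and scoring as the CTS versions for parental violence". That outcome is reported by children and by teachers.

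Data analyses, Quantitative outcomes, puts these scores into mixed models and tests the time-by-intervention interaction as the main research question.

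Nowhere does the article recode response 6, set it aside as a separate category, or dichotomise the items. It does state recoding for several secondary scales (quality of life, adult–child relationship, perceived stress, school climate and decision making).

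**The concern.** Three statements do not fit together: code 6 means the act did not occur in the past week, item scores are summed, and a higher sum means more violence. Under the printed rule, an act that happened once long ago adds more to the total than the same act happening repeatedly this week.

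The intervention aims to stop these acts, and follow-up is about 12 weeks after delivery. An act that has stopped by then is accurately described by response 6. The more often the training succeeds in this way, the more items in the intervention arm move to the top code. The bias therefore runs against the intervention and can reverse the sign of the estimate. It reaches violence by parents and by teachers, from every reporter.

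The labels of 0 and 6 also overlap. An act that happened earlier but not in the past week satisfies both, so identical histories can score 0 or 6 depending on how the respondent or interviewer reads the options.

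**Working it through.** The plan states no figure that depends on this scoring, so there is none to reproduce. The check applies the printed rule and compares it with the same rule after counting 6 as 0.

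**Inputs from the article:** codes 0 to 6, plain sum, higher = more violence; 9 physical, 7 emotional and 5 emotional-maltreatment items.

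**Assumption:** codes 1 to 5 are rising past-week frequencies. Their labels are not given; the related witnessing items under Normative beliefs about violence run from 0 to 5 in that way. Code 6 is the top code whatever the labels are.

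**1. Score ranges.** As written the maxima are 9×6 = 54, 7×6 = 42 and 5×6 = 30. With 6 counted as 0 they are 45, 35 and 25.

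**2. One respondent, nine physical items, all acts stop and are answered 6.**

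| Baseline code on every item | Baseline sum | Follow-up as written | Change as written | Change with 6 as 0 |
|---|---|---|---|---|
| 1 | 9 | 54 | +45 | −9 |
| 2 | 18 | 54 | +36 | −18 |
| 3 | 27 | 54 | +27 | −27 |
| 4 | 36 | 54 | +18 | −36 |
| 5 | 45 | 54 | +9 | −45 |

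The sign is reversed in every row.

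**3. Group means (illustrative).** Assume 70% of the nine acts were ever experienced, half of those were active in the past week at mean code 2.1, all others ever experienced are answered 6, and half of the active acts stop.
- Baseline: 9×0.7×0.5 = 3.15 active items and 3.15 at code 6. Past-week score: 3.15×2.1 = 6.6. As written: 6.6 + 3.15×6 = 25.5.
- Follow-up: 1.575 active and 4.725 at code 6. Past-week score: 1.575×2.1 = 3.3. As written: 3.3 + 4.725×6 = 31.7.

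**4. Standardised size.** Add two assumptions: items are independent, and codes 1 to 5 carry weights 40, 30, 15, 10 and 5% (mean 2.1, mean square 5.8).
- Baseline variance of the past-week score: 9×(0.35×5.8 − 0.735²) = 13.4, SD 3.66. Change −3.31/3.66 = −0.90 SD.
- Baseline variance as written: 9×(0.35×5.8 + 0.35×36 − 2.835²) = 59.3, SD 7.70. Change +6.14/7.70 = +0.80 SD.

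| Ever experienced | Of those, active in past week | Past-week score | As written |
|---|---|---|---|
| 70% | 50% | −0.90 SD | +0.80 SD |
| 70% | 30% | −0.65 SD | +0.45 SD |
| 50% | 50% | −0.73 SD | +0.58 SD |
| 90% | 60% | −1.25 SD | +1.38 SD |

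**5. How many stopped acts would have to be answered 0?** If a share r of stopped items is answered 0 and the rest 6, the mean change per stopped item is 6(1 − r) − m, where m is its mean baseline code. This is negative only if r > 1 − m/6: 83% at m = 1, 67% at m = 2, 50% at m = 3, 33% at m = 4, 17% at m = 5.

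**The case against.** The strongest reply is that the article may describe the response options and leave out a recode. It speaks of item scores and does not say these are the raw response codes. Its own reading of a higher score as more violence makes sense only if 6 is not the top value. The provision for zero-inflated outcomes and count models also sits more easily with response 6 counted as zero. A recode may exist in the analysis plan or in the cited adapted versions of the scale, which are not shown. This bears on what the authors intend, but it does not rescue the text. A scoring rule is stated, it contains no recode, and the article does state recoding for other scales.

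The second reply is that the reversal is conditional, and this stands as a limit on size. Some respondents whose violence has stopped may choose 0. If violence becomes less frequent but still occurs in the past week, no item moves to 6, and the printed score falls just as the corrected one does. The group illustration assumes both full cessation of half of the active acts and an answer of 6 for each. The standardised figures also assume exposure rates, independent items and the meaning of codes 1 to 5. They show what can happen and do not forecast this trial's bias. Still, cessation weighs heavily: at baseline code 2, one stopped item answered 6 adds 4 points, which cancels four items that each drop from 2 to 1.

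The safeguards in the analysis section do not help. Winsorising leaves the coding unchanged, and a sum that includes a categorical 6 is not a count.

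**Conclusion.** The concern holds: the scoring rule as printed is wrong for every primary outcome. That each stopped act answered 6 raises the score follows from the stated coding, sum and direction alone. The size depends on assumptions. For a respondent whose nine physical acts all stop and are answered 6, the change is +9 to +45 where it should be −45 to −9. In the group scenarios, true falls of 0.65 to 1.25 SD appear as rises of 0.45 to 1.38 SD. Less cessation, or more stopped acts answered 0, would shrink the distortion and could leave a diluted effect in the right direction. Because the primary result can change sign, this must be settled before the data are analysed.

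**What to change.** - State that response 6 counts as 0 before summing, in the child, parent and teacher versions of the CTS and at both visits. The past-week scores then run 0–45 (physical) and 0–35 (emotional), and 0–25 for the five emotional-maltreatment items if they are scored.
- Report earlier occurrence (response 6) as a separate descriptive indicator.
- Give the labels of codes 1 to 5, and say whether 0 means that the act has never happened at all. Once 6 counts as 0, the overlap between the two labels no longer affects the past-week score.

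The cost is one scoring sentence and one line of recode syntax. Responses recorded by code can be rescored without loss, and no new data are needed. The rule should be fixed before any comparison by arm, so that it cannot be taken for a choice made after seeing the results.

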##### Teachers’ violence

An adapted version of the CTS [3, 63, 64] will be used to assess the emotional and physical violence by teachers at school, captured through both children’s and teachers’ self-reports. The CTS will include 9 items on physical violence, 7 items on emotional violence. For children’s report, 2 additional purpose-built items on witnessed violence by teachers will be assessed. The teacher version uses the same answer scale and scoring as the CTS versions for parental violence (c.f., for more details outcome description about parental violence). Previous studies in East Africa assessing teachers’ violence revealed acceptable psychometric properties [14, 66, 67].

In addition, during the quantitative interview 4 CTS-items will be body mapped by asking the children where on their body they experienced the emotional (shout & threaten) and physical (hit & pinch) violent act by teachers. The affected body parts will be documented on a sheet of paper with a body-icon. Promising results for body mapping have been shown for trauma research in the context of refugees [65].

#### Secondary quantitative outcomes

##### Attitudes towards violence

Favorable attitudes towards physical and emotional violence will be assessed from parents and teachers with an adapted version of the CTS [3, 63, 64]. Sixteen items are formulated as a statement beginning with “When children/students do something wrong, I think it is OK to …”. Each item ends with the respective act of physical or emotional violence. The items are answered on a 4-point Likert scale ranging from 0 (never OK) to 3 (always or almost always OK). Subscale items are then sum scored for each parent or teacher with higher values indicating parent’s or teacher’s more favorable attitudes towards physical or emotional violence. The adapted CTS was used before to assess teachers’ self-reported attitudes towards violent discipline in Tanzania [3, 23].

##### Children’s mental health problems

The children’s emotional and behavioral problems will be assessed with the short version of the Pediatric Symptom Checklist – Youth Report (PSC-17-Y) [68, 69]. PSC-17-Y includes 17 items rated on a 3-point Likert scale ranging from 0 (never true) to 2 (often true). These items will be summed up to a total score of emotional and behavioral problems ranging from 0 to 34. The PSC-17-Y will be answered by the children and parents [68]. Good psychometric properties have been shown in adapted PSC-versions in a sample of HIV-infected children in Botswana [70] as well as for school children in Uganda [71].

